#### Power

Our planned sample, including attrition, will provide sufficient power to test linear effects on teacher- and classroom school-level variables with a minimum detectable effect size (MDES) of small to medium effects, *d* = 0.37. We used PowerUp! [100] assuming clustering, final samples of 46 schools evenly randomized to condition, 6 teachers per school (after 15% attrition), school ICCs of 0.10 (consistent with our pilot data), and 13 timepoints. With the same assumptions as above, plus an assumption that 50% of the schools will be in a given moderator subgroup, our MDES for detecting any single school-level moderator variable is 0.48 and teacher-level moderator variable is 0.45. For mediator analyses, PowerUp! identifies power using the Sobel test, joint test, and Monte Carlo simulations. Across all tests, we will have a power of greater than 0.80 to detect reasonable and likely effects, based on our pilot trial and standard interpretations of effect sizes. We will detect an MDES equivalent to Cohen’s *d* = 0.60 for the treatment-mediator pathways (e.g., BASIS-T to implementation intention) which is lower than our actual obtained effect size from the pilot trial (which ranged from *d* = 0.61 to 1.16 for our primary mediators), an MDES of Pearson’s *r* = 0.3 for the mediator-outcome path (e.g., implementation intention to student behavior, a small effect), and an MDES of *d* = 0.10 for the direct path from treatment to student outcome.

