**Methods:**

This project uses a blocked randomized cohort design with an active comparison control (ACC) condition. We will recruit and include approximately 276 teachers from 46 schools randomly assigned to BASIS-T or ACC conditions. Aim 1 will evaluate the main effects of BASIS-T on proximal implementation mechanisms (attitudes, subjective norms, self-efficacy, intentions to implement, and maintenance self-efficacy), implementation outcomes (adoption, reach, fidelity, and sustainment), and child outcomes (SEB, attendance, discipline, achievement). Aim 2 will examine how, for whom, under what conditions, and how efficiently BASIS-T works, specifically by testing whether the effects of BASIS-T on child outcomes are (a) mediated via its putative mechanisms of behavior change, (b) moderated by teacher factors or school contextual factors, and (c) cost-effective.

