### Participants and recruitment

Teachers from schools in the USA will be recruited to participate. Inclusion criteria include being a teacher at an elementary (typically K–5th grade or K–8th) school and not having been trained or supervised in delivering PGD in the past 5 years. We will recruit approximately 276 teachers from 46 elementary schools in the USA. The final balance of teachers and schools is dependent on recruitment, with the goal of meeting minimum statistical power. Schools will be approached to participate via multiple routes, including leveraging existing relationships and networks, educational listservs, and posting on social media. Interested school representatives may respond using the interest survey linked in flyers or by contacting the research team via email. The generalizer (generalizer.org), a free, web-based tool for selecting schools for randomized controlled designs that are statistically representative of a chosen inference population, will also be used to help assure the representativeness of our sample [58]. Strata will be created on urbanicity, school race/ethnicity, school percent female, school percent free and reduced lunch, school size, school percentage English language learners, and the number of schools in the district.

Once schools have been selected, teacher recruitment will proceed for both cohorts of schools with the assistance of site administrators. Principals will provide us with the email addresses of teachers in their schools. Research staff or school leadership will contact eligible participants by email or phone to describe the purpose of the study, research procedures, and incentives. Informed consent will be collected online prior to training (Additional file 3) and teachers will be free to decline participation. Monetary incentives will be provided to participating teachers and schools.

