#### Data analytic plan

Basic data screening and descriptives will be conducted for all quantitative variables. We will explore and statistically adjust for baseline equivalence between conditions on all individual outcomes and all school, teacher, and student variables following established guidelines [83]. For all longitudinal modeling, the statistical adjustment will use baseline intercepts as random terms; for dissimilar outcome domains, non-equivalent baseline variables will be included as covariates. Data missing at random will be modeled using full information maximum likelihood estimation or multiple imputation as appropriate.

Unless otherwise indicated, quantitative analyses will employ mixed-effects models using time points nested within classrooms within the school. Standard model-building procedures will be used [84, 85]. Classroom and time trends will be allowed to randomly vary. Piecewise time models will estimate slopes from T1 to T4 (training), T5 through T6 (first month of post-training implementation), T7–T11 (first academic year), and T12–T13 (sustainment during the subsequent year). Variables for condition and condition x time will be added, and iterative models with possible control variables will be tested. Covariates not contributing at *p* < 0.10 based on likelihood ratio tests will be removed. Level 2 and 3 predictors will be fit and excluded for the same reasons. We will obtain estimates of whether there were statistically significant differences among the groups on the rate of change over time (i.e., slope) and whether there are statistically significant group differences in the average score on each outcome variable at the final timepoint of each piecewise segment. Models will be generalized, with appropriate link functions (e.g., log-link, Poisson) applied based on distributional form (e.g., dichotomous, zero-inflation). Estimation will be fit using full maximum likelihood. Models will be assessed for possible violations of assumptions. Goodness-of-fit will be evaluated using likelihood ratios, deviance statistics, and fit criteria. The inference will be evaluated relative to *p* < 0.05. For RQs with multiple DVs, we will adjust for the false discovery rate using Benjamini and Hochberg’s procedure [86].

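### The MDES of 0.37 assumes 6 teachers per school after 15% attrition, but the recruitment target of 276 teachers leaves only 5.1 per school

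*Protocol article*

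**What the plan says.** The recruitment section states: "We will recruit approximately 276 teachers from 46 elementary schools in the USA". The Methods paragraph of the abstract agrees: "We will recruit and include approximately 276 teachers from 46 schools randomly assigned". The recruitment section adds that the final balance depends on recruitment, with the aim of reaching minimum statistical power.

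The Power section says that the planned sample, attrition included, gives an MDES of d = 0.37 for linear effects on teacher-, classroom- and school-level variables. The PowerUp! inputs are "final samples of 46 schools evenly randomized to condition, 6 teachers per school (after 15% attrition), school ICCs of 0.10" (the ICC being described as in line with the pilot data) "and 13 timepoints". It states no covariate R-squared, no within-teacher correlation and no number of sides.

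The Data analytic plan sets the threshold at p < 0.05, also without naming one or two sides. It tests group differences in slope and in the average score at the last timepoint of each piecewise segment.

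**The concern.** The same number, 276, serves both as the teachers to be recruited and as the teachers left after 15% attrition. Both cannot hold. A recruiting team could stop at 276 believing that attrition is already covered, when the power calculation assumed a sample that this target does not deliver.

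The figure is also offered for teacher, classroom and school variables in general. Many Aim 1 outcomes are measured once, or are tested at a single end-of-segment occasion. For those the listed school and teacher numbers do not lead to 0.37 under a two-sided test without covariates.

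**Working it through.** **Step 1: the head count**

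- At recruitment (abstract; Participants and recruitment): 276 / 46 = 6.0 per school.
- After 15% attrition: 276 × 0.85 = 234.6, about 235; 234.6 / 46 = 5.1 per school.
- To retain 6 per school: 276 / 0.85 = 324.7, about 325 recruited (7.1 per school), which is 49 more than the stated target.

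**Step 2: reproducing 0.37**

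Inputs from the Power section: J = 46 schools, half per arm, n = 6, school ICC ρ = 0.10. Alpha of 0.05 comes from the Data analytic plan. Power of 0.80 is assumed for the headline figure, because the section names 0.80 only in its mediator text. R-squared is taken as 0 because none is stated.

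Two-level formula: MDES = M × SE, with SE = √[4ρ/J + 4(1−ρ)/(Jn)] and M the sum of the t quantiles for alpha and for power on J − 2 = 44 df.

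- SE at n = 6: √(0.4/46 + 3.6/276) = 0.1474. SE at n = 5.1: √(0.4/46 + 3.6/234.6) = 0.1551.
- M = 2.530 one-tailed and 2.865 two-tailed.

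A three-level version for the mean of 13 timepoints, with an assumed share s of total variance between teachers within schools, uses SE = √{4[0.10/46 + s/(46n) + (0.90 − s)/(46n × 13)]}. The share is not in the article. At s = 0.52, SE is 0.1291 for n = 6 and 0.1344 for n = 5.1.

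| Model | n = 6 | n = 5.1 | Change |
|---|---|---|---|
| Two-level, one-tailed | 0.373 | 0.392 | 0.019 |
| Mean of 13 timepoints, two-tailed, s = 0.52 | 0.370 | 0.385 | 0.015 |
| Two-level, two-tailed | 0.422 | 0.444 | 0.022 |

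Over s = 0.3 to 0.8, the 13-timepoint model runs from 0.336 to 0.409 at n = 6 and from 0.346 to 0.430 at n = 5.1.

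Covariates are a further route. In the two-tailed two-level model with n = 6, R-squared at both levels of 0.22 gives 0.373 and 0.24 gives 0.369, so about 0.23 reproduces 0.37. At n = 5.1 the same values give 0.393 and 0.388.

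**Step 3: the single-occasion, two-sided case**

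Without covariates the MDES is 0.42 at n = 6 and 0.44 at n = 5.1. From the noncentral t distribution, power to detect d = 0.37 is then about 69% and 65%.

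**Step 4: which outcomes Step 3 describes**

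Under Quantitative surveys, times 1 and 2 precede the pre-training session, teacher-rated classroom behaviour starts at time 4, and attendance, discipline, grades and test scores are requested at the end of each school year. Self-reported fidelity runs over times 4 to 13. Adoption is first analysed as a single proportion. A mean over 13 occasions therefore does not describe these outcomes, nor does it match the end-of-segment comparisons in the Data analytic plan.

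**The case against.** A reader might infer that 0.37 came from a one-tailed test, since 0.373 fits well, and that the design really gives 0.44. The documents support neither. The Power section lists 13 timepoints as an input, the analysis uses three-level longitudinal models with baseline adjustment, and schools are matched on baseline mechanisms. A two-tailed 0.37 with 6 teachers per school is reachable through a teacher variance share near 0.52 or an R-squared near 0.23, and neither value is extreme. Dropping the two pre-intervention timepoints barely matters: with 11 occasions and s = 0.52 the MDES moves from 0.370 to 0.371.

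It is also fair that sidedness, R-squared and within-teacher correlation are details a condensed article may leave to the full protocol. Their absence is not the fault raised here. Full information maximum likelihood would recover part of the information from teachers who leave, but the Power section itself counts retained teachers, so the comparison has to be made on that basis.

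The attrition effect is small because precision depends mainly on the 46 schools. The pilot effects quoted for the primary mediators, d = 0.61 to 1.16, exceed even 0.44. The target is approximate and tied to reaching adequate power, so 276 is not a fixed stopping number. And d does not apply directly to adoption, which is a proportion and a time to event.

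What remains is the head count. A gap of 49 teachers is more than the word approximately can cover, and the text gives one number two incompatible meanings.

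**Conclusion.** The contradiction is certain on the face of the text: 276 cannot be both recruited and retained under 15% attrition. If 276 is the number recruited, the MDES is understated by about 0.015 to 0.02 under each of the models tabulated.

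Separately, for a two-sided single-occasion comparison without covariates, the listed schools, teachers and ICC give 0.42, or 0.44 at 5.1 teachers per school. This rests on 80% power, 44 df and no covariate gain. Most of the distance from 0.37 to 0.44 comes from assuming that two-sided, single-occasion model rather than from attrition. So 0.44 should be read as the figure for that class of outcome and not as the sensitivity of the whole design. Likewise, about 65% power for d = 0.37 belongs to that case only. Which route produced 0.37 cannot be settled from the article.

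**What to change.** - State in the abstract, in Participants and recruitment and in Power whether 276 is recruited or retained.
- If recruited, recompute the MDES with 5.1 teachers per school. If retained, change the recruitment target in the abstract and in Participants and recruitment to about 325.
- Beside the restated MDES, name the model, the number of sides, and any R-squared or within-teacher correlation used.
- Give a separate figure for continuous outcomes measured once or tested at the end of a segment: about 0.44 two-sided without covariates at 5.1 per school.

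The cost is a recalculation and a text correction, best made before recruitment closes. No further teachers are needed if the less favourable MDES is accepted; holding 6 per school after attrition would mean recruiting about 49 more.

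### The school-level moderator MDES of 0.48 and the direct-path MDES of 0.10 are inconsistent with the main-effect MDES of 0.37 given in the same paragraph

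*Protocol article*

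**What the plan says.** All the figures stand in one paragraph of the protocol article, under Power.

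- Main effect: a "minimum detectable effect size (MDES) of small to medium effects, *d* = 0.37".
- Sample behind that figure: "final samples of 46 schools evenly randomized to condition", with 6 teachers in each after allowing for attrition.
- Clustering and repeated measures: "school ICCs of 0.10 (consistent with our pilot data), and 13 timepoints".
- Moderator inputs: "With the same assumptions as above, plus an assumption that 50% of the schools will be in a given moderator subgroup".
- Moderator result on that basis: the article reports that "our MDES for detecting any single school-level moderator variable is 0.48 and teacher-level moderator variable is 0.45".
- Mediation: three path values, namely d = 0.60 for treatment to mediator, r = 0.3 for mediator to outcome, and a third, also called an MDES, of "0.10 for the direct path from treatment to student outcome".

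The section states power above 0.80 for the mediator analyses. It gives no sidedness, teacher-level ICC or covariate R². The Data analytic plan gives a 0.05 significance level, also without sidedness. Under Randomization, schools are the unit of assignment.

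**The concern.** An interaction between two balanced school-level factors is estimated less precisely than the main effect of either one, by a fixed factor. The stated step from 0.37 to 0.48 is a ratio of 1.30, which is too small for that factor. The direct-path figure goes the other way. It is less than a third of the main-effect MDES, although both are contrasts between the same two sets of 23 schools.

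These figures tell the reader what Aim 2 can detect: school-level moderation in RQ2b and the mediation model in RQ2a. If they are wrong, the stated sensitivity of those analyses is better than the design delivers.

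**Working it through.** **Inputs from the Power section:** J = 46 schools (23 per arm), n = 6 teachers per school, school ICC ρ = 0.10, 13 timepoints, 50% moderator split. **Assumed:** alpha 0.05 two-sided (one-sided also shown), power 0.80 for every MDES, no covariates, and a teacher-level ICC ρ_t between 0.3 and 0.7 where repeated measures are modelled.

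**Formulas.** MDES = M × SE, where M is the sum of the t quantiles for alpha and for power.

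- V (two-level) = ρ/J + (1 − ρ)/(Jn)
- V (three-level) = ρ/J + ρ_t/(Jn) + (1 − ρ − ρ_t)/(13Jn)
- Main effect: SE² = 4V, df = J − 2 = 44, M = 2.865 two-sided
- School-level moderator, 50% split: SE² = 16V, df = J − 4 = 42, M = 2.868 two-sided

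**Step 1: reproduce 0.37.**

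- Two-level, two-sided: V = 0.10/46 + 0.90/276 = 0.00543, so 2.865 × √0.02174 = 0.42.
- The same, one-sided: 0.373.
- Three-level, two-sided, ρ_t = 0.5: V = 0.10/46 + 0.5/276 + 0.4/3,588 = 0.00410, so 2.865 × √0.01639 = 0.367.

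So 0.37 is attainable under standard variants and can serve as the anchor.

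**Step 2: school-level moderator.** Each arm-by-moderator cell holds a quarter of the schools, so the SE ratio is √(16V/4V) = 2. V cancels, and with it the ICC, cluster size, timepoints and any common R².

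- Anchored on 0.37: main-effect SE = 0.37/2.865 = 0.129, and the moderator MDES = 2 × 0.129 × 2.868 = 0.74.
- Power at a true moderator effect of 0.48 (noncentral t, SE 0.258, two-sided): about 44%.

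| Variant, no covariates | Main effect | School-level moderator |
|---|---|---|
| Two-sided, three-level, ρ_t 0.3 to 0.7 | 0.34 to 0.40 | 0.67 to 0.79 |
| Two-sided, two-level (timepoints ignored) | 0.42 | 0.85 |
| One-sided, three-level, ρ_t 0.3 to 0.7 | 0.30 to 0.35 | 0.59 to 0.70 |
| One-sided, two-level | 0.373 | 0.75 |

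Mixing a two-sided 0.37 with a one-sided moderator test still gives 0.65. The effect within one subgroup of 23 schools, two-sided with ρ_t = 0.5, is 0.53. Working back from 0.48, the main-effect MDES would be 0.48/2 = 0.24. Keeping the 0.37 anchor, 0.48 would need 46 × (0.74/0.48)² ≈ 109 schools.

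**Step 3: direct path.**

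- School variance alone (unlimited teachers and waves): 2.865 × √(4 × 0.10/46) = 0.27 two-sided, 0.24 one-sided.
- No clustering at all, 276 teachers, two-sided: 0.34.
- Error variance to be removed to go from 0.37 to 0.10: 1 − (0.10/0.37)² = 93%. A mediator-outcome correlation of 0.3 explains 0.3² = 9%.
- Power at d = 0.10 with SE 0.129: about 12%.
- Schools needed, anchored on 0.37: 46 × (0.37/0.10)² ≈ 630.
- Only treating all 46 × 6 × 13 = 3,588 teacher-timepoints as independent comes close (0.094).

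**Step 4: teacher-level moderator.** With a fixed slope and ρ_t = 0.4, SE² = 16 × (0.4/276 + 0.5/3,588) = 0.0254, giving 0.449. The range is 0.40 to 0.57 for ρ_t from 0.3 to 0.7. The stated 0.45 is attainable.

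**The case against.** The other side has four fair arguments.

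1. **Impossibility.** A reader might infer that 0.48 is out of reach for any trial with 46 schools. The documents do not support that. Sidedness is unstated, the Data analytic plan allows baseline adjustment and covariates, and schools are paired before assignment. The school-variance limit for the moderator is 0.53 two-sided but 0.47 one-sided, just under 0.48. Covariates with R² near 0.67 at both levels would also bring the moderator to about 0.48. What survives is the inconsistency: those same covariates would move the main effect to about 0.24, and one-sided testing leaves the factor of 2 unchanged.

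2. **Teacher-level figure.** A reader might extend the criticism to the 0.45, since it shares a sentence with the 0.48. That would be wrong. It is reproduced with the 13 timepoints and a plausible teacher-level ICC, and an article may leave that ICC to a fuller document.

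3. **The 0.10 may be an input.** It closes a list of three path values for a mediation power run based on Sobel, joint and Monte Carlo tests, so it may be an assumed effect size. This is a reasonable reading, and it would reduce the repair to a relabelling. But the text calls the value an MDES that the trial will detect, and that statement is wrong as it stands.

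4. **Consequences.** A reader might infer that the plan will treat a non-significant direct path as full mediation, or a null moderator as evidence of no moderation. No section states either rule. RQ2a in the Data analytic plan describes path analysis of mediation and gives no direct-path criterion. The harm is limited to misstated sensitivity.

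**Conclusion.** The point holds as an internal inconsistency of moderate severity. If the main-effect MDES is 0.37, the school-level moderator MDES is about 0.74, and 0.48 would be detected with about 44% power. Across the no-covariate variants the moderator figure runs from 0.67 to 0.85 two-sided and from 0.59 to 0.75 one-sided. The factor of 2 needs only a common effect metric, common sidedness and the stated 50% split.

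A direct-path MDES of 0.10 cannot stand beside 0.37. Without covariates the school-variance limit is 0.24 to 0.27, and the stated mediator-outcome correlation supplies nowhere near the 93% variance reduction required. Power at 0.10 is about 12%.

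The power values assume two-sided alpha 0.05 and the 0.37 anchor. The 0.80 power for the non-mediation figures is also an assumption. The Aim 1 main-effect figure is not challenged. The affected analyses all belong to Aim 2, which is why the severity is moderate.

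**What to change.** - Restate the school-level moderator MDES as about 0.74. Alternatively, restate the main-effect and moderator figures together under one declared set of inputs (sidedness, power, teacher-level ICC, covariate R² at each level).
- For the direct path, either replace 0.10 with an MDES of about 0.37, or describe 0.10 as an effect size assumed in the mediation power calculation and not as a detectable effect.
- Leave the teacher-level 0.45 as it is.

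The cost is a few restated figures in one paragraph. Sample size, models and Aim 1 are unchanged. The downside is a less favourable stated sensitivity for Aim 2.

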## Discussion

### Innovation

This hybrid type 3 trial will contribute to the literature on pragmatic implementation strategies, as well as nascent but expanding literature on implementation mechanisms [101–103]. Aside from BASIS-T’s counterpart strategy, BASIS-C [104], no studies of strategies have been explicitly designed to impact TPB and HAPA mechanisms while testing those mechanisms via mediation models. Recent systematic reviews [103] indicate that much more work is necessary surrounding implementation strategy mechanisms to allow for the development of streamlined, pragmatic approaches to improving implementation outcomes that can be generalized across EBPPs. The current study also contributes significantly to theory-building in implementation by exploring factors beyond TPB and HAPA that help to explain hypothesis-defying residuals’ relationships between mechanisms and behavior.

In addition, this project will examine the costs and cost-effectiveness of the BASIS-T strategy. Cost-effectiveness is an important driver of adoption decisions, especially at system and policy levels [105]. Examination of cost-effectiveness is particularly critical for implementation strategies designed with pragmatism in mind. Efficient delivery and impact are key components of pragmatism, as are clear links between prioritized implementation determinants (e.g., self-efficacy in BASIS-T) and strategy components [106].

### Limitations

This study uses a block randomization approach in which all participating teachers in each school are randomized to either BASIS-T or the ACC condition. Although our team considered randomizing at the individual teacher level to align with the individual focus of the BASIS-T strategy, we opted against this because it presented a significant risk of contamination because of the extent to which some of BASIS-T’s putative mechanisms are likely to be socially influenced (especially subjective social norms).

